# Minimally Invasive Dentistry Based on Atraumatic Restorative Treatment to Manage Early Childhood Caries in Rural and Remote Aboriginal Communities: Protocol for a Randomized Controlled Trial

**DOI:** 10.2196/10322

**Published:** 2018-07-25

**Keywords:** cost-effectiveness analysis, early childhood caries, health utility, health-related quality of life

## Abstract

**Background:**

The caries experience of Aboriginal children in Western Australia (WA) and elsewhere in Australia is more than twice that of non-Aboriginal children. Early childhood caries (caries among children <6 years) has a significant impact on the quality of life of children and their caregivers, and its management is demanding and commonly undertaken under general anesthesia. A randomized controlled trial using a minimally invasive dentistry approach based on Atraumatic Restorative Treatment (ART) in metropolitan Perth, WA, has demonstrated a significant reduction in the rate of referral to a dental specialist for dental care among children with early childhood caries, potentially reducing the need for treatment under general anesthesia. The tested approach was clinically successful and was without adverse effects on child dental anxiety. The model of ART-based primary care requires further testing and development if similar outcomes for Aboriginal children in remote and rural settings are to be achieved.

**Objective:**

The study aims to develop, implement, and evaluate a remote primary care model to deliver effective primary dental services, encompassing treatment and preventive services, to Aboriginal preschool children (based on minimally invasive approaches including ART).

**Methods:**

This is a two-arm parallel cluster randomized controlled study in which a test group will be provided with the intervention treatment at the start of the study and a control group will be provided with the intervention treatment 12 months after study commencement (delayed intervention). Participating communities, stratified by size of community (ie, number of children in the sample frame) and baseline caries experience, will be randomly assigned using a computer-generated block randomized list into immediate (test group) or delayed intervention (control group; provided with standard care). Informed consent will be obtained from all participants. Aboriginal research assistants will explain the study to the parents and assist the parents in completing the questionnaires. Participants in the randomized study will be examined at baseline and at 12 months follow-up by a calibrated examiner. Test group participants will subsequently be contacted and appropriate appointments coordinated for treatment. Control group participants will be provided with standard preventive care by the Aboriginal Health Workers and managed for treatment as per standard procedures.

**Results:**

Community consultations have been undertaken and 26 communities have agreed to participate. Fieldwork is in progress to recruit study participants.

**Conclusions:**

The significance of the study lies in its holistic approach to testing the model of care. Clinical evaluations as well as oral health‒related quality of life evaluations will be undertaken. Cost-effectiveness and cost-utility evaluations will assist in the development of policy options for oral health services for rural and remote communities. The elicitation of caregiver perspectives through focus group interviews will supplement the clinical, psychosocial, and cost-utility evaluations and provide a richer evaluation of the intervention.

**Trial Registration:**

Australian New Zealand Clinical Trials Registry ACTRN12616001537448; https://www.anzctr.org.au/Trial/Registration/TrialReview.aspx?id=371735 (Archived by WebCite at http://www.webcitation.org/70UMxndFZ)

**Registered Report Identifier:**

RR1-10.2196/10322

## Introduction

### Background

Dental caries in early childhood, or early childhood caries (ECC), has been shown to have a significant impact on the quality of life of children and their caregivers [1]. These effects include symptoms of pain, functional limitations, psychological dysfunction, parental distress, and financial burden. Also, early life dental caries experience is a strong predictor of dental caries in adulthood [2]. Thus, preventive interventions in the early life course are expected to affect oral health in older age. Therefore, interventions at an early age to manage disease in its early stages and effective preventive measures are needed to maintain function and quality of life and to improve oral health in adulthood.

### Managing Dental Caries in Early Childhood

Oral rehabilitation for dental caries under general anesthesia (GA) of children with ECC has been shown to improve child oral health‒related quality of life (COHRQoL) [3]. However, dental treatment under GA does little to prevent the occurrence of new dental decay in these children and they are often readmitted for dental treatment under GA [4]. Thus, treatment and preventive approaches that can be undertaken in primary dental care settings to reduce the number of preschool children undergoing dental GA are urgently required. There is limited information available on COHRQoL outcomes in children after primary dental care for dental caries that suggests modest improvements in COHRQoL [5]. Therefore, there is a need to evaluate changes in COHRQoL after primary dental care.

Comprehensive care under GA is relatively expensive, for the individual and for the community, and is not without risks, including the potential for long-term adverse neurodevelopmental effects [6-8]. Also, recent reports suggest that oral rehabilitation under GA for children does little to alleviate dental fear or change noncooperative behavior and may in fact heighten child dental fear [9,10].

### Potentially Preventable Hospitalizations

Admissions to a hospital for dental care are classified as potentially preventable with timely and adequate non-hospital care [11]. However, there is a trend of increasing hospital admissions for dental care among children, especially among 0-4-year-olds [12,13]. In Australia, this is occurring in spite of the apparent low dental caries experience among children [14,15]. Admissions to hospital for dental conditions made up more than 20% of total admissions for potentially preventable acute admissions in 2013-14 in Australia, second only behind admissions for urinary tract infections [16]. In a recent report, Western Australia (WA) had the highest, and an increasing, rate of hospital admission for dental treatment of all Australian States and Territories among children. Worryingly, the rate among Australian Aboriginal children was twice that of non-Aboriginal children among the 0-4-year-olds [12]. The cost for hospital admission for dental care for children in WA has been estimated at approximately Aus $9-10 million per year. The mean cost for Indigenous children was significantly higher than the cost of care for non-Indigenous children [6].

### Aboriginal Oral Health

A recent report on the oral health of school children examined within the School Dental Service (SDS) in WA showed that Aboriginal children had nearly twice the decay experience of non-Aboriginal children in both deciduous and permanent teeth, and 1.8 times and 2.4 times the number of carious deciduous and permanent teeth, respectively, after controlling for exposure to community water fluoridation and socioeconomic level [17]. Also, although the rate of admission for hospital-based care has increased for Aboriginal children and is now approaching the rate of non-Indigenous children, it is lower for Aboriginal children in rural and remote areas. This has been attributed to lack of access to care due to costs, availability of services, and a lower proportion of Aboriginal children with dental insurance [6].

In WA, nearly two-thirds of the Aboriginal population lives in rural and remote locations, making access to services challenging [18]. The WA Aboriginal Health and Wellbeing Framework identified oral health among the priorities addressing risk factors, along with development of health services tailored to meet the needs of the Aboriginal people underpinned by evidence, based on quality research [18]. The proposed research will evaluate a model of care, which can be translated into mainstream health service delivery, using a strong randomized controlled study design.

### A “New” Approach to Dental Caries Management in Early Childhood

The minimally invasive dentistry approach to managing dental caries and its potential role in the provision of public dental services has been described in dental literature [19]. The Atraumatic Restorative Treatment (ART) approach, initially developed to assist dental care delivery in underserved communities, where access to electricity and running water may not be readily available, is now increasingly seen to have relevant applications in subpopulations around the world [20]. Whereas the standard care approach would involve the administration of local anethesia and removal of dental caries using rotary instruments, the ART approach principally relies on removing affected dentine using hand instruments alone, usually without the administration of a local anesthetic, and restoration of the prepared cavity with a glass-ionomer cement. ART makes provision of dental treatment in very young children, where cooperation for standard dental care approach may be limited, feasible in a primary care setting. It may also reduce dental anxiety among children, thereby facilitating appropriate future dental attendance behaviors [21].

### Evidence

In WA, dental therapists, through the SDS and working in school-based dental clinics, have been the mainstay of successful publicly provided dental care for 5-17-year-old school children since the early 1970s [22]. A recently completed pilot randomized controlled trial in WA showed that primary care delivered by dental therapists trained in the ART approach, compared to standard care (ie, dentists providing treatment using the drill and local anesthesia), reduced the rate of referral for specialist pediatric dental care of preschool children affected by ECC by 44% [23]. The ART-based approach adopted in the study relied on treating carious teeth by removing affected dentine using hand instruments without the administration of local anesthetic. However, a pragmatic approach to treatment was undertaken in that the use of rotary instruments was permitted where a clinician judged that the child was able to cope with the procedure after a period of acclimatization to dental treatment. This pragmatic approach enabled the undertaking of more invasive procedures, beyond what standard ART approach encompassed, such as pulp therapy of deciduous teeth and, in a few instances, tooth extractions.

The study also included a range of preventive interventions including fluoride varnish application to deciduous molars and noncavitated carious lesions as well as oral health counseling using the motivational interviewing approach. The study delivered a “holistic” package of care that considered the needs of the child in total, including preventive care and appropriate skill development of the parent/caregiver to promote oral health. Also, in that study, some children who were scheduled for care under GA were able to be successfully treated using the ART-based approach. The study showed that the COHRQoL was improved after primary dental care with acceptable clinical outcomes [24,25] without adverse effects on childhood dental anxiety. In addition, the approach was cost saving. Hence, the ART-based approach may provide a successful primary model of care, encompassing both treatment and prevention, for children in rural and remote locations where access to GA may not be advisable or readily available.

### Current Situation

The WA state government is introducing an early childhood preventive program for preschool children (0-4-year-olds) in rural and remote Aboriginal communities by applying fluoride varnish to the primary teeth by Aboriginal health workers trained in the fluoride varnish application. The fluoride varnish program is incrementally being rolled out throughout WA, starting in Kimberley (north-west WA) in 2016. The program is a preventive program, and children requiring dental treatment are referred to the local dental practitioners, either private practitioners or practitioners within the Health Department or Aboriginal Medical Services. While fluoride varnish application has been shown to be efficacious in ECC prevention among Aboriginal children [26], children without adequate access to treatment services may continue to experience untreated disease.

Currently, preschool children (ineligible for SDS care) requiring dental treatment need to source care from private dental practitioners (ie, at their own cost) or, if eligible for subsidized care (ie, liable for co-payments) through government general dental clinics, where restorative care is provided by dentists. Dental therapist and oral health therapists provide mainly dental hygiene services. Subsidized dental care is available to those who are in receipt of certain types of Commonwealth Government benefits (eligibility for the benefits are means tested). The WA government general dental clinics, located mainly in regional cities and major towns, provide clinical care mainly to eligible adults, but children ineligible for SDS and in receipt of specific types of government benefits are able to access care. The location of these clinics in major regional centers means extensive travel for children living in more remote locations to access care. Also, treatment is usually provided using standard care approaches involving the administration of a local anesthetic and using rotary instruments to prepare the cavity.

### Why is this Study Important?

Provision of dental care to preschool children poses significant challenges because of the stage of development and capacity for cooperation of the young child, and treatment is often provided under GA. The issues are multiplied for Aboriginal preschool children in rural and remote locations where access to specialist dental care is severely limited. Alternative approaches to dental treatment of dental decay in preschool children in primary dental care settings that reduce the need for GA is urgently required. This study will test the hypothesis that Aboriginal preschool children in rural or remote locations can be provided with appropriate dental care using the ART-based approach, without the need for specialist care and can potentially avoid the need for GA.

Our study has six major strengths: (1) it will further develop and evaluate the ART-based model of care, which had been successfully tested in a pilot program in an urban setting in WA, led by author PA, (2) we will develop, for the first time, a dental specific child health utility scale, (3) we will measure the change in clinical parameters as well as the changes in child quality of life and health utility with dental treatment, (4) we will measure the impact of dental treatment on child dental anxiety, (5) we will undertake a cost-effectiveness/cost-utility analysis, and (6) we will ascertain the community acceptability of the tested intervention through focus group interviews. The “holistic” evaluation of the intervention including efficacy and effectiveness of the clinical intervention as well as impact on psychosocial parameters and economic evaluation will greatly facilitate research translation. Also, our research team comprise both world-class researchers who have experience working with the Australian Aboriginal population, and leading policy and service delivery experts, thus ensuring the translation of the study findings into applicable policy, practice, and service delivery in rural and remote locations. We will also be working in collaboration with an Indigenous Advisory Committee and significant community members to provide oral health promotion training to significant community members. This will embed oral health promotion within the communities and ensure sustainability of the oral health improvements after the research has been concluded.

The Kimberley region of WA is geographically large, three times the size of the United Kingdom. Almost the entire region of Kimberley (97%) is classified by the Australian Bureau of Statistics as Very Remote with the remaining 3% as Remote. It also has a higher proportion of Aboriginal people than the rest of the state (45% vs 3.6%). There are hundreds of Aboriginal communities dotted throughout the region, and most are very small with few people. The estimated resident population of the region in 2016 was 36,392 (children 0-4 years was 3274). The region also has high levels of socioeconomic disadvantage with the majority of residents (57%) living in areas with the lowest 10% of the Index of Relative Socio-Economic Advantage and Disadvantage score in Australia [27].

### Aims

The principal aim of the proposed study is to develop, implement, and evaluate a remote primary care model to deliver effective primary dental services, encompassing treatment and preventive services, to Aboriginal preschool children (based on minimally invasive approaches including ART). This will be compared with standard care for cost and benefits in terms of improved dental health and reduced childhood dental anxiety. Our specific aims and hypotheses are:

Aim 1. Measure the proportion of children able to be provided with care without the need for dental specialist referral and the increment in dental caries. Hypothesis: The proportion of children successfully managed without specialist referral and without new dental caries will be higher in the test group compared with the control.

Aim 2. Develop a dental-specific health utility scale and measure the change in childhood health utility. Hypothesis: The change in health utility will be greater in the test group compared with the control.

Aim 3. Undertake an economic evaluation of the intervention. Hypothesis: The test intervention will have either less costs with greater/similar health gain or affordable incremental costs for additional unit of health outcomes.

Aim 4. Measure the change in childhood oral health-related quality of life. Hypothesis: The child oral health-related quality of life in the test group will be better than the control

Aim 5. Evaluate the acceptability of the ART-based care through focus group interviews. Hypothesis: The ART-based care will have greater acceptability than the control.

## Methods

### Study Design

We will undertake a two-arm parallel cluster randomized controlled study in which a test group will be provided with the intervention treatment at the start of the study and a control group will be provided the intervention treatment 12 months after study commencement (delayed intervention) in the Kimberley region of WA.

### Ethics

Ethics approval for the study has been provided by the University of Adelaide, Human Research Ethics Committee (HREC) (Ethics approval No. H-2017-015), and the Western Australia Country Health Service HREC (Project Reference #2017/01) and the WA Aboriginal Health Ethics Committee (Project Reference #790).

### Recruitment

We will adopt successful recruitment strategies applied in a wide body of research undertaken by author LJ in her work (unpublished) with Aboriginal communities in South Australia and the Northern Territory. This has included extensive engagement with Aboriginal communities and active community participation in the research process. We will engage with community elders through linkages established by authors DA and RM who both have a long association with Aboriginal communities in the Kimberley region. We will employ local Aboriginal people as research assistants to facilitate with community engagement and participant recruitment guided by a senior project officer based in Kimberley. Participant recruitment will be a two-step process: (1) elicit specific communities to participate, and (2) elicit individual participation. A Senior Research Officer appointed to coordinate the project with the assistance of an Aboriginal research assistant will meet with the Chief Executive Officers of individual Aboriginal communities to explain the proposed study to invite community participation in the study. An Aboriginal Advisory Group with representation from all the Aboriginal Controlled Health Organisations in Kimberley will also be formed to provide appropriate guidance to the research team and assist with information dissemination and participant recruitment. Individual participant recruitment will use active engagement with community members at locations where study participants are likely to gather, such as visits to early childhood learning facilities, community general store, local community women’s functions, and through word-of-mouth dissemination of project information. Parents and guardians will provide signed informed consent after being provided with information about the study and the processes undertaken to protect and preserve data confidentiality.

Parents and children aged 0-4 years, residing in selected communities in the Kimberley region of WA will be eligible. Children with complex medical conditions or developmental syndromes would be excluded. All other children within the scope for age and who consent to participate will be recruited.

Participating communities, stratified by size of community (ie, number of children in the sample frame) and baseline dental caries experience, will be randomly assigned using a computer-generated block randomized list into immediate (test group) or delayed intervention (control group, given standard care) by a central study coordinator. We will select communities for recruitment based on available information on community population from various sources (eg, Community CEOs, the WA Country Health Service, Australian Bureau of Statistics). Communities will also be far enough apart to minimize contamination of test and control (at least 50 km). We will invite participation from communities with at least 100 people to ensure likelihood of recruiting at least 15 children in the age group of interest. We will stratify the communities on size of population and dental caries experience (high vs low; data obtained at baseline examination). Parents of all children of eligible age will be provided with information and consent forms and a questionnaire to complete (Aboriginal research assistants will explain the study to the parents and help parents complete the questionnaires). After receipt of signed consent, participants in the randomized study will be contacted for a baseline clinical examination by a calibrated examiner. After baseline examination, all participants will be contacted by the trial coordinator and appointments arranged for those allocated into the early treatment group. Test group participants will subsequently be contacted and appropriate appointments coordinated to be seen at the local SDS clinics or field clinic settings for treatment. Control group participants will be provided with standard preventive care by the Aboriginal Health Workers and managed for treatment as per standard procedures.

Study participants will be reviewed after 12 months from baseline and will undergo a clinical examination and complete a follow-up questionnaire. Figure 1 shows the study’s participant flow chart.

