### Sample Size

A recently completed pilot study in WA, which compared ART-based care against standard care, reported a nine-fold difference in the proportion of children referred for specialist pediatric dentist care (5% vs 49%). A conservative difference in effect size of 2.5 was assumed to estimate the sample size (10% vs 25%). The intracluster correlation was estimated from the dental caries experience of Aboriginal children participating in a NHMRC Project Grant (1010758)‒funded cluster randomized trial (.05). Using these parameters, with 15 clusters available in each arm of the trial, the estimated sample size required, at 80% power and alpha of .05, was 165 in each arm of the trial with 11 children per cluster. Allowing for loss to follow-up of 25%, the estimated sample size is 220 per arm of the study or 15 children per cluster. The recently completed pilot trial in WA, undertaken by author PA, achieved 90% retention of study participants after 12 months, while an oral health promotion intervention undertaken by author LJ among an Aboriginal population achieved 80% retention of study participants. The estimated sample size will have sufficient power to detect a 33% difference in mean ECOHIS at 90% power and alpha of .05.

The study timeline is shown in Table 2. It is expected that community engagement will take the bulk of the first year in recognition of the challenges of undertaking research in northwestern WA, which is as far as Sydney is from Perth (about 3000 km). Participant recruitment and treatment provision is similarly expected to take up to 2 years because of constraints of locations of communities and weather conditions.

**Table 2 table2:** Study timeline, indicated by actions taken per quarter.

Action	Year 1				Year 2				Year 3				Year 4				Year 5			
	1	2	3	4	1	2	3	4	1	2	3	4	1	2	3	4	1	2	3	4
Community engagement, staff recruitment, training, ethics approval, printing	✓	✓	✓	✓																
Participant recruitment, baseline, examinations, randomization, commence treatment, baseline data entry			✓	✓	✓	✓	✓	✓	✓	✓										
Follow-up examinations, focus group interviews, delayed intervention group treatments							✓	✓	✓	✓	✓	✓	✓	✓	✓					
Data entry, data clean-up, data analyses									✓	✓	✓	✓	✓	✓	✓	✓	✓			
Report preparation, community presentation and feedback																	✓	✓	✓	✓

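### The 100-person community floor does not secure the 15 children per cluster that the sample size needs: the protocol's regional age share gives about 9 per 100 residents

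*Protocol article*

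**What the plan says.** Three parts of the protocol article bear on this point.

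- **Recruitment.** Invitations go to "communities with at least 100 people to ensure likelihood of recruiting at least 15 children in the age group of interest". On age, "Parents and children aged 0-4 years, residing in selected communities in the Kimberley region of WA will be eligible". Two things then reduce the head count: "Children with complex medical conditions or developmental syndromes would be excluded", and, of the rest, "All other children within the scope for age and who consent to participate will be recruited". The same section stratifies communities by size, measured as the count of children in the sampling frame.
- **Why is this Study Important?** The description of the Kimberley gives the only demographic figures: "The estimated resident population of the region in 2016 was 36,392 (children 0-4 years was 3274"; "It also has a higher proportion of Aboriginal people than the rest of the state (45% vs 3.6" (both percentages); and, of the region's Aboriginal communities, "most are very small with few people".
- **Sample Size.** With 10% versus 25% referred, an intracluster correlation of 0.05, 15 clusters per arm, 80% power and alpha 0.05, the plan needs 165 children per arm, or 11 per cluster. After 25% loss to follow-up, "the estimated sample size is 220 per arm of the study or 15 children per cluster".

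**The concern.** Recruiting 15 children from 100 people requires at least 15% of residents to be aged 0-4, with every one of them eligible and consenting. The region's share is 9.0%. The floor is the only stated safeguard for a cluster size that enters the power calculation directly. If it lets in communities that supply well under 15 children, and larger communities do not make up the difference, the trial falls short of 220 per arm. Its clusters will also vary more in size, which costs efficiency at a given total.

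**Working it through.** **Inputs.** From Why is this Study Important?: 36,392 residents, 3274 aged 0-4, 45% Aboriginal. From Recruitment: floor of 100 people, target of 15 children. From Sample Size: 10% versus 25%, ICC 0.05, 15 clusters per arm, 25% loss. Assumed, because not stated: a two-sided test, and consent rates of 75%, 80% and 100%.

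**1. The plan's own figure.** Comparing 10% with 25% under individual randomization (pooled normal formula) needs 100 per arm. The design effect at m = 11 is 1 + (11 − 1) × 0.05 = 1.50. That gives 150 per arm without continuity correction, and 113 × 1.50 = 169.5 with it. With 15 clusters fixed, the cluster formula that adds one cluster per arm requires 15.04 clusters at m = 10 and 14.20 at m = 11. So m = 11 is the smallest size that fits, and 15 × 11 = 165. Then 165/0.75 = 220, and 220/15 = 14.7, rounded to 15. The stated sample size reproduces.

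**2. Yield of the floor at the regional share.**
- Share aged 0-4: 3274/36,392 = 9.0%, so 100 people hold about 9 children. That is 40% below 15, and below the 11 to be analysed.
- Residents needed for 15 children: 15/0.08996 = 167 at full participation; 167/0.80 = about 208 at 80% consent; 167/0.75 = about 222 at 75% consent.

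**3. How much higher the share could be in Aboriginal communities.** Aboriginal residents number 0.45 × 36,392 = 16,376. If every child aged 0-4 in the region were Aboriginal, their average share would be 3274/16,376 = 20.0%. That is the ceiling for the average; a single community could differ.

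What the 100-person rule requires on average:

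| Consent | Share aged 0-4 needed | Region's 0-4s who would be Aboriginal | Share aged 0-4 left among other residents |
|---|---|---|---|
| 100% | 15% | 0.15 × 16,376/3274 = 75% | 4.1% |
| 80% | 15/0.80 = 18.75% | 94% | 1.0% |
| 75% | 15/0.75 = 20% | 100% | about 0% |

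**4. Illustrative power if every cluster sat at the floor.** Analysed per cluster: m = 100 × share × consent × 0.75. Effective size per arm: 15m/(1 + (m − 1) × 0.05). Power is from the pooled normal approximation for 10% versus 25%.

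| Share | Consent | m | Effective n per arm | Power |
|---|---|---|---|---|
| 9% | 100% | 6.75 | 78.6 | 70% |
| 12% | 100% | 9.00 | 96.4 | 79% |
| 15% | 100% | 11.25 | 111.6 | 84% |
| 9% | 80% | 5.40 | 66.4 | 63% |
| 12% | 80% | 7.20 | 82.4 | 72% |
| 15% | 80% | 9.00 | 96.4 | 79% |

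The planned 15 × 11 gives an effective 110 per arm and 84% by the same formula. A noncentral t with 28 degrees of freedom gives slightly lower values: 68% instead of 70% in the first row, and 82% for the planned design.

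**The case against.** A reader might infer that the floor cannot yield 15 children, or that the trial's power is really about 70%. The documents support neither reading.

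- **The 9.0% is not the share in the clusters.** It covers all residents of a region that is 55% non-Aboriginal, while the clusters are Aboriginal communities. The protocol's figures allow an average of up to 20 children per 100 there. Fifteen per 100 is unsupported, not impossible.
- **The protocol speaks of likelihood, not a guarantee.** That is fair, but a likelihood also needs some basis, and the document offers none.
- **A floor is not a mean.** The sample size needs about 15 enrolled on average. Larger communities can offset small ones, and actual sizes are not given.
- **The planned size has some slack.** By the pooled formula, 80% power with 15 clusters per arm needs 100 × 0.95/(15 − 100 × 0.05) = 9.5 analysed, or about 13 enrolled at 25% loss. Sample Size also cites 80% and 90% retention in earlier studies. At those rates 12 enrolled per cluster would give 80.5% to 83.4%.

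All four limit how far the point reaches. None supplies the missing justification: once an assumed 20-25% of families decline, the rule needs a share at or near the ceiling of the protocol's own figures. The power figures in the working are not lower bounds either. Larger communities raise power, while refusals, exclusions and unequal cluster sizes lower it.

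The Results section reports 26 communities agreed, against the 30 assumed. That is a separate shortfall and is not counted here.

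**Conclusion.** The point holds as an unsupported planning assumption at odds with the only age data in the document. The Sample Size arithmetic itself is sound. What is not shown is that the selection rule delivers the cluster size fed into it: at the regional share the floor yields about 9 children where 15 are wanted.

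The consequence for power depends on three things the document does not give: the age share in the invited communities, the consent rate, and the distribution of community sizes. If every cluster sat at the floor with full consent, power would run from about 70% to 84% as the share goes from 9% to 15%. That is a scenario and not a forecast. The remark that most communities in the region are very small makes clusters near the floor a real prospect, but it does not describe those that were invited.

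**What to change.** Express the floor as a minimum number of eligible children aged 0-4 in each community. Recruitment already names a child count as a stratification variable, so the quantity is foreseen, although the article does not say the counts are in hand. Alternatively, keep the population floor and state the age share and consent rate that justify 15 recruited per 100 residents.

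Then restate the expected number enrolled and analysed per cluster, and the power, from the actual child counts, using a design effect that allows for unequal cluster sizes.

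The work is a recalculation and a change of wording, once child counts are obtained for the communities. The real cost is that the stated cluster size and power may become less favourable.
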